### Statistical Analysis

Baseline measurements will be presented using descriptive statistics. The participants will be block randomized, and the groups should therefore be equal in age and gender distribution. The groups will be compared with regard to clinically relevant variables to ensure they are comparable. Because of the limited size of the groups, they may differ on some variables and, when such variables are identified, they will be adjusted for in the statistical analyses, for example, by treating them as possible confounders.

Baseline data will be compared with data from the normal population (HUNT 3 study) to assess whether our sample is representative of the entire population of Norwegian individuals living with diabetes.

The differences in the main outcome between baseline and 4 months and between baseline and 1 year will be compared between the three groups. First, the crude difference will be analyzed using analysis of variance with post hoc tests (differences between groups). The difference between baseline and the following two measurements within each group will be analyzed using a *t* test. When a change in a selected outcome variable is identified, this change will be modeled using linear regression adjusted for possible confounders.

The cost-effectiveness data will be analyzed using standard statistical analyses depending on the distribution of the data. Missing values will be replaced by imputation. Mean values and 95% CI will be reported for each component of resource use as well as for total costs and effectiveness. Sensitivity analyses will be conducted to handle nonsampling variation.

Our study has a longitudinal design and we expect some dropouts. Therefore, we will perform two analyses: one based on intention to treat and another based on the participants who actually participated actively in our study (per protocol).

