### Randomization

Patients who meet our inclusion criteria sign the informed consent form, complete the self-reported questionnaire, and are randomized into one of the three groups through block-randomization in the start-up meeting described above. Randomization is performed through the Center of Randomization at the Unit for Applied Clinical Research at the Norwegian University of Science and Technology in Trondheim, using WebCRF (Case Report Form). Immediately after randomization, the patients are told which group they have been placed. Those placed in the intervention groups are given a mobile phone with the self-management application in the same meeting and taught how to use the phone and the application. Those randomized to both the application and the health counseling group is given information about this intervention at the end of the same meeting. The reason for choosing this procedure is to save time for those who travel a considerable distance to participate.

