### Primary Outcome Measure

The primary outcome is the difference between the control group and the intervention groups regarding change in HbA1c level after 4 months and after 1 year. When possible, HbA1c levels are recorded within 2 weeks before or after the expected date of follow-up (ie, within a 1-month window) [56]. HbA1c level has been shown to vary between 100 laboratories in the United Kingdom and between the various HbA1c assays in use [57]. In the present study, patients are included from different GP offices, and there may be variations in HbA1c levels recorded. To avoid bias potentially introduced through the use of different HbA1c assays, the DCA Vantage Analyzer from Siemens is used when possible.

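### The only unconditional between-group analysis of HbA1c is a crude ANOVA of change; covariates, baseline HbA1c included, enter only through data-dependent triggers, and block randomization is wrongly said to equalise age and gender

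*Protocol article*

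**What the plan says.** The primary outcome, under Primary Outcome Measure in the protocol article, is the between-group difference in change in HbA1c at 4 months and at 1 year. The Statistical Analysis section says how it will be tested:

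- **Quantity compared.** "The differences in the main outcome between baseline and 4 months and between baseline and 1 year will be compared between the three groups".
- **First analysis.** "the crude difference will be analyzed using analysis of variance with post hoc tests (differences between groups"). This is the only between-group analysis of the main outcome that will be run regardless of what the data show.
- **First route to adjustment.** The groups are compared on clinically relevant baseline variables. They may differ on some because they are small, and "when such variables are identified, they will be adjusted for in the statistical analyses".
- **Second route to adjustment.** "When a change in a selected outcome variable is identified, this change will be modeled using linear regression adjusted for possible confounders".
- **Premise about balance.** "The participants will be block randomized, and the groups should therefore be equal in age and gender distribution".

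The Randomization section says only that patients "are randomized into one of the three groups through block-randomization in the start-up meeting described above", through an external randomization center. It names no stratification factor. Nowhere does the article list a covariate set, and baseline HbA1c is not named as a covariate.

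**The concern.** Four things are wrong with the rule as written.

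1. **Imbalance is a poor reason to adjust.** Under valid randomization, any baseline difference is chance. It says nothing about whether the variable predicts HbA1c. Covariates should be chosen for prognostic value, before the data are seen.
2. **The second route is also data-dependent.** Adjustment follows once a change has been found. So both whether to adjust and what to adjust for can depend on results.
3. **Baseline HbA1c is left to these routes.** It is already collected and is the obvious predictor of later HbA1c. A change score does not remove baseline imbalance: whenever the regression slope of follow-up on baseline is below 1, an arm that starts higher by chance tends to fall further.
4. **The balance inference does not follow.** Blocking balances group sizes. It controls age or gender only when carried out within strata of those factors.

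At stake are the precision of the HbA1c comparison, its exposure to chance baseline differences, and a reader's confidence that the reported model was not picked afterwards.

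**Working it through.** **Inputs from the article.** Difference 0.35, SD of the outcome variable 0.5, two-sided 5%, power 80%, 34 per group, 50 per group after the dropout allowance (Power Analyses); 26 of 151 lost so far (Results).

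**Assumed.** The correlation r between baseline and follow-up HbA1c is not given; I use 0.3, 0.5, 0.7 and 0.9. Because the outcome is change, I read the SD of 0.5 as the SD of change. Baseline and follow-up variances are taken as equal (s²).

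**Step 1: the plan's own figure.** n = 2(1.960 + 0.842)² × 0.5² / 0.35² = 32.04, so 33 per group by the normal approximation. The two-sample t solution is 33.02, rounded up to 34. The stated 34 reproduces, reading 0.35 as a raw difference.

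**Step 2: precision.** Var(change) = 2s²(1 − r). Var(baseline-adjusted) = s²(1 − r²). The ratio is (1 + r)/2. Power uses 42 per arm, since (151 − 26)/3 = 41.7, and residual SD 0.5 × √[(1 + r)/2].

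| r (assumed) | Variance ratio | Extra patients the change score needs (1/ratio − 1) | Power, change score | Power, adjusted |
|---|---|---|---|---|
| 0.3 | 0.65 | 54% | 0.89 | 0.98 |
| 0.5 | 0.75 | 33% | 0.89 | 0.96 |
| 0.7 | 0.85 | 18% | 0.89 | 0.93 |
| 0.9 | 0.95 | 5% | 0.89 | 0.90 |

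With unequal variances, Var(change) − Var(adjusted) = (s_x − r·s_y)², where s_x and s_y are the baseline and follow-up SDs. This is never negative, so apart from one degree of freedom adjustment does not lose precision.

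**Step 3: exposure to chance imbalance.** An SD of change of 0.5 implies s = 0.5/√[2(1 − r)]. At 50 per arm, one standard error of the baseline difference is s√(2/50). The expected shift in the change-score difference is (1 − r) times that.

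| r | s | 1-SE imbalance | Shift | Share of 0.35 |
|---|---|---|---|---|
| 0.3 | 0.423 | 0.085 | 0.059 | 17% |
| 0.5 | 0.500 | 0.100 | 0.050 | 14% |
| 0.7 | 0.645 | 0.129 | 0.039 | 11% |
| 0.9 | 1.118 | 0.224 | 0.022 | 6% |

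**Step 4: behaviour of the rule.** This was simulated for one pair of arms, 42 per arm, r = 0.3 to 0.7, 20,000 trials per setting. The article gives no criterion for imbalance, so p < 0.05 is assumed.

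- Adjusting only when baseline HbA1c looks imbalanced: type I error 0.040 to 0.046, power 0.89 to 0.90. Almost none of the gain in Step 2 is recovered.
- If either the crude or the adjusted result may be claimed: type I error 0.066 (r = 0.7) to 0.078 (r = 0.3).
- In trials where baseline HbA1c is imbalanced, the crude test rejects a true null in 12% (r = 0.7) to 24% (r = 0.3).

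**Step 5: the balance premise.** With 50 per arm, no stratification and an assumed 50% women, the 95% range of a chance gender difference between two arms is ±1.96√(2 × 0.25/50) = ±0.196, or about 20 percentage points either way.

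**The case against.** The best defence has several parts.

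- **The crude ANOVA is fixed in advance and unbiased over repeated randomizations.** This stands. A reader might infer that the HbA1c comparison is biased or its test invalid; the plan does not support that. In the simulation the crude test, averaged over all trials, holds 5% under the null.
- **Imbalance is not the only way in for covariates.** Also correct: regression after an identified change is a second route. It rescues nothing, because it too waits on the data.
- **The article never labels either analysis primary, and an unseen analysis plan may do so.** The missing label is no finding. But the triggers are stated rules, and a fuller plan would have to contradict them, not fill them in.
- **The balance sentence is hedged, and a condensed article may omit stratification factors.** It does say that groups should be equal and then that they may differ. A reader might infer that the blocks were certainly unstratified; the article does not show that. What is wrong is the inference from blocking alone.
- **The size is uncertain.** True: r is not given, and at r = 0.9 the gain is small. Two larger claims are tempting. Setting a baseline SD of 1.0 beside r of 0.5 to 0.7 gives a shift of 17% to 29% of 0.35. But with an SD of change of 0.5, a baseline SD of 1.0 forces r = 1 − 0.5²/(2 × 1.0²) = 0.875, so those values cannot hold together. Likewise, a 40% chance of at least one spurious imbalance (1 − 0.95¹⁰) needs ten independent variables screened at p < 0.05, and the article states neither the number nor the threshold.

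**Conclusion.** The point holds as a matter of efficiency and pre-specification, and the plan should be changed. It does not make the trial's main comparison invalid.

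The crude change-score analysis has 1.05 to 1.54 times the variance of a baseline-adjusted one for r from 0.9 down to 0.3. With the plan's own 0.35 and 0.5, the power forgone at 42 per arm is about 1 to 9 percentage points. A one-standard-error imbalance in baseline HbA1c moves the crude estimate by 6% to 17% of the target difference. These sizes rest on the assumed r, on 0.5 being the SD of change, and on equal variances at the two visits. The inflation of type I error to about 7% or 8% applies only if the choice between crude and adjusted results is left open after both are seen; the article does not say that both may be claimed, but it sets no order of precedence.

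The faults that need no assumption are the two data-dependent triggers, the absence of baseline HbA1c as a fixed covariate, and the inference from blocking to balance in age and gender.

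**What to change.** In the Statistical Analysis section:

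1. Make the main between-group model, at 4 months and at 1 year, HbA1c at follow-up regressed on arm and baseline HbA1c. Using change as the response with the same covariate gives the same arm effect.
2. Name any further covariates, for example age and sex, before analysis. Use them whatever the baseline table or the crude result shows.
3. Delete both triggers: adjustment upon observed imbalance, and adjustment upon an identified change.
4. Keep the crude ANOVA as a supportive analysis and say that the adjusted model takes precedence.
5. Reword the balance sentence to say that blocking balances group sizes. If randomization was stratified, state the factors and include them in the model.

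The cost is a few sentences. Baseline HbA1c, age and sex are already collected, and no patients or procedures are added. The article reports 11 patients still in the trial and results yet to come, so on its own account the model could still be fixed before analysis.

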### Trial Population and Recruitment

Persons with T2D are eligible to participate in the study if they are older than 18 years, were diagnosed with diabetes for more than 3 months before the study inclusion, and have an HbA1c level >7.0%. Patients must be cognitively able to participate, understand, and be able to complete questionnaires in Norwegian language, and be able to use the mobile self-management system provided to the intervention groups. The exclusion criteria are any mental or physical conditions that interfere with the protocol.

Patients treated in primary care from both the southern and northern parts of Norway are recruited by their general practitioners (GPs). The GPs obtain recruitment information from the research team and are asked to recruit eligible patients to the study. Patients are also recruited from “diabetes start courses” held by the specialist health care service, which are offered to those newly diagnosed with diabetes in Norway by local public health clinics in municipalities and by advertisement. Patients willing to participate in the study are first given a letter with a brief summary of the study and an invitation to obtain more in-depth information about the study and implications. This information is given both orally and in written form in start-up meetings arranged by the project team. Before entering the study, all patients are required to provide written informed consent about their participation. All patients included must be under the care of a GP who adheres to national guidelines for diabetes care.

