### Evaluation Measures

#### Overview

Our evaluation is based on the Model for Assessment of Telemedicine (MAST), which is a framework developed for the evaluation of the TM interventions in RENEWING HEALTH [39]. We are also using principles from the complex intervention framework developed by the Medical Research Council in the United Kingdom [52]. We intend to evaluate a large number and variety of outcomes. The consolidated standards of reporting trials (CONSORT) statements for reporting parallel group randomized trials are followed [53,54]. The study data include responses on self-reported questionnaires, logs from the Few Touch application, and data collected from patient journals obtained from the GPs. To assess the representativeness of the sample, we will use data from the general population with and without diabetes from the Nord-Trøndelag Health Study (HUNT 3) in Norway [55]. We will also conduct in-depth interviews with patients and health care providers consecutively. In addition, we will collect data from the technical support service to get knowledge about who are using the service, frequency of use, and what they are asking for. Further, we collect notes from the diabetes nurse taken during the health counseling. The measures in our study are described in detail below.

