#### Physical Activity

Measures of physical activity are collected by the same questions as in the HUNT 3 study for comparison purposes with a diabetes sample from the general population. We have also included one question based on the transtheoretical stages of change to assess the respondents’ motivation toward physical activity and change in activity level [66].

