The patients included in the study may represent those who are open to new technology and who are willing to participate in a complex intervention; thus, the acceptability to using such devices may be lower in the wider population. It will be important to assess representativeness. In Norway, we have data from large population-based studies that are well suited for comparison purposes. Recruitment to RCTs is also frequently problematic [73,74], and one concern in the present RCT is whether patients who are eligible will be disappointed when they are randomized to the control group and not to an intervention group receiving the Few Touch application or the application together with health counseling. There is reason to question whether an RCT is suited to this type of study when we are recruiting possibly motivated patients to participate in a TM intervention and they may be randomized to the control group. Different designs that are more flexible and clinically useful have been discussed [73], and our study may contribute to this discussion, which is of current interest.

In the present study, we have chosen HbA1c level as the primary outcome. Many people with diabetes have poor understanding of their HbA1c level, and only few remember their actual test results. The level of agreement between perceived glycemic control and actual HbA1c values is also poor [75]. This could be a challenge in our research when the primary outcome is a measure of which many patients may have a poor awareness and understanding. In addition, glycemic control may not be a goal for some patients when they volunteer for the study. However, the patients in the intervention groups will have access to information about their blood glucose measures through the Few Touch application, and one of the intervention groups will additionally receive health counseling to help them attain self-management and diabetes control.

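### The representativeness check takes everyone living with diabetes as its target, although only adults with type 2 diabetes and HbA1c >7.0% could enter, so on HbA1c, diabetes type and variables linked to them it mixes eligibility with volunteer selection

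*Protocol article*

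**What the plan says.** All references are to the protocol article.

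- **Target.** Under Statistical Analysis, baseline data are set against HUNT 3, described there as the normal population, "to assess whether our sample is representative of the entire population of Norwegian individuals living with diabetes".
- **Comparator.** The Overview under Evaluation Measures says that, for representativeness, "we will use data from the general population with and without diabetes", taken from HUNT 3. The Physical Activity section says its questions match HUNT 3 "for comparison purposes with a diabetes sample from the general population". Neither place limits the comparator by diabetes type or HbA1c.
- **Entry.** Trial Population and Recruitment states: "Persons with T2D are eligible to participate in the study if they are older than 18 years". They must also be people who "were diagnosed with diabetes for more than 3 months before the study inclusion, and have an HbA1c level >7.0" per cent. They must be able to complete questionnaires in Norwegian and to use the mobile system.
- **Purpose.** The Discussion notes that participants may be unusually open to technology and to a complex intervention, so that acceptability may be lower in the wider population. It concludes: "It will be important to assess representativeness".

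**The concern.** The stated target contains people who could never have been enrolled: those with type 1 diabetes and those with HbA1c at or below 7.0%. Any gap between the sample and that target has two sources. One is eligibility, which the trial imposed and which is known in advance. The other is volunteering, which the Discussion wants to learn about. The planned comparison reports only their sum.

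At stake is the generalisability statement. A raised baseline HbA1c, or differences in treatment or complications that go with it, could be taken as evidence of an unrepresentative sample when they only reflect the entry rules. The reverse can also happen: a volunteer effect in the opposite direction could cancel the eligibility effect and make the sample look representative. The study says it is meant to help decision makers choose technologies, so this statement has some weight.

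**Working it through.** **The plan's own figures.** The plan gives no figure for this check. Its only design calculation, 34 per group (Power Analyses), concerns the randomised comparison. It reproduces: 2 × (1.960 + 0.842)² × 0.5² / 0.35² = 32.04, so 33 by the normal approximation; the exact t calculation gives power 0.7997 at 33 and 0.812 at 34. It plays no further part here.

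**Step 1: target against entry criteria.**

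| Characteristic | Stated target | Trial sample |
|---|---|---|
| Diabetes type | any | type 2 only |
| HbA1c | any | >7.0% only |
| Time since diagnosis | any | more than 3 months |
| Norwegian questionnaires, ability to use the system | not required | required |

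Differences on the first two rows are built in, provided the reference includes type 1 diabetes and values at or below 7.0%.

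**Step 2: size of the built-in HbA1c shift.** Assumption, because the documents give no distribution: HbA1c in the diabetes population is normal with mean m and SD s. With a = (7.0 − m)/s, the mean among those above 7.0 is m + s × φ(a)/(1 − Φ(a)).

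Worked case, m = 7.0 and s = 1.2: a = 0, φ(0)/(1 − Φ(0)) = 0.3989/0.5 = 0.798, and the mean is 7.0 + 1.2 × 0.798 = 7.96, a rise of 0.96.

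| m | s | Share above 7.0 | Mean above 7.0 | Rise |
|---|---|---|---|---|
| 6.5 | 0.8 | 27% | 7.49 | 0.99 |
| 6.5 | 1.2 | 34% | 7.80 | 1.30 |
| 6.5 | 1.5 | 37% | 8.03 | 1.53 |
| 7.0 | 0.8 | 50% | 7.64 | 0.64 |
| 7.0 | 1.2 | 50% | 7.96 | 0.96 |
| 7.0 | 1.5 | 50% | 8.20 | 1.20 |
| 7.5 | 0.8 | 73% | 7.86 | 0.36 |
| 7.5 | 1.2 | 66% | 8.16 | 0.66 |
| 7.5 | 1.5 | 63% | 8.40 | 0.90 |

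The rise is 0.36 to 1.53 points with no volunteer selection. Its direction does not depend on normality: removing the values at or below 7.0 always raises the mean.

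**Step 3: is the shift visible?** The trial has 151 patients. The size of the HUNT 3 reference is not given; 500 and 2,000 are assumed. Dividing the rise by √(truncated SD²/151 + s²/n_ref) gives z of about 6 to 27 over all scenarios, well beyond sampling error.

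**Step 4: why the two effects cannot be separated.** Observed gap = eligibility shift + volunteer shift. Take m = 7.5, s = 0.8, where eligible patients average 7.86. Volunteers who average 7.86 show a gap of 0.36 although they are typical of eligible patients. Volunteers who average 7.50 show no gap in means although they lie 0.36 below eligible patients.

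**Step 5: variables not tied to the entry criteria.** For a standardised difference d, power is about Φ(d/√(1/151 + 1/n_ref) − 1.96). For d = 0.3 and n_ref = 500: √(0.00662 + 0.00200) = 0.0929, 0.3/0.0929 = 3.23, and Φ(1.27) = 0.90. Over n_ref = 300 to 2,000, power is 85 to 94% for d = 0.3 and 52 to 66% for d = 0.2. On such variables the check can detect moderate differences.

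**The case against.** The strongest reply is that the check covers baseline data generally, including sex, education, working status and physical activity, and that nothing forces a difference on these. That stands. A reader might infer that the entry criteria alone make the whole check fail, or that it cannot reveal volunteer selection at all. The documents do not support this: failure is built in only for HbA1c and diabetes type, and elsewhere the comparison is at worst confounded.

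Four further points also stand, at least in part:

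- The Discussion itself speaks of the wider population, so a broad comparison is not plainly the wrong question. It does not, however, make the whole diabetes population a suitable main benchmark for a sample cut at 7.0%.
- The Physical Activity section refers to a diabetes sample, and nothing says that people with and without diabetes would be pooled. Pooling should not be read into the text.
- Ability to use the system overlaps with the openness to technology that the check should reveal, so it is not purely an artefact.
- It is tempting to set the HbA1c shift against the 0.35 in Power Analyses. That figure sizes a between-arm comparison and is no yardstick for an external baseline comparison.

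It could also be said that choosing a subgroup of the reference belongs in a fuller plan. That does not answer the point, because the article writes out the target population, and that target is wider than the trial could sample.

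**Conclusion.** The concern holds in limited form. The target named under Statistical Analysis is wider than the eligible population. A difference is therefore forced on HbA1c and diabetes type, and on variables linked to them eligibility cannot be separated from volunteering. The forced rise in mean HbA1c is about 0.4 to 1.5 percentage points. This rests on an assumed normal distribution with mean 6.5 to 7.5% and SD 0.8 to 1.5, none of which the documents give. On variables not tied to the entry criteria the check keeps its value. Severity is low: the randomised comparison and the primary result are untouched, and only the external-validity statement is at risk.

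**What to change.** In Statistical Analysis and in the Overview under Evaluation Measures:

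1. Name the target as Norwegian adults with type 2 diabetes and HbA1c >7.0%.
2. Make the main representativeness comparison with HUNT 3 respondents who meet the recorded entry criteria: type 2 diabetes, age, time since diagnosis and, if HUNT 3 holds it, HbA1c >7.0%.
3. Keep any comparison with the whole diabetes population, or with people without diabetes, as descriptive context, and state that differences on entry-criterion variables are expected.
4. If HUNT 3 lacks HbA1c, keep the type 2 restriction and do not interpret HbA1c differences as non-representativeness.
5. Acknowledge that ability to use the app and Norwegian-language ability cannot be matched.

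The cost is a reworded target, a restriction of the reference data and a smaller comparator group. No new trial data are needed. The documents do not say which of these variables HUNT 3 records, so that must be confirmed first.

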#### Power Analyses

Power analyses were performed before recruitment to estimate the sample size needed based on the HbA1c level as the primary outcome. Given an effect size of 0.35, a significance level of 5%, a standard deviation of the outcome variable of 0.5, statistical power of 80%, and a two-tailed significance test, the sample size was estimated to be 34 individuals in each group. To compensate for dropouts, the sample was set to 50+50 (two intervention groups), and 50 in the control group. A total of 151 patients were included.

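### The confounder-adjusted regression is fitted only after a change has been seen, with trigger and outcomes undefined, so which adjusted estimates exist depends on the results

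*Protocol article*

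**What the plan says.** All of this is in the Statistical Analysis section of the protocol article unless another section is named.

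- **Baseline imbalance.** Because the groups are small, they may differ on some variables. The section says, with no condition on the outcome result, that such variables will be adjusted for.
- **Crude between-group comparison.** Changes in the main outcome from baseline to 4 months and to 1 year are compared between the three groups, first by ANOVA with post hoc tests. No condition is attached.
- **Within-group tests.** "The difference between baseline and the following two measurements within each group will be analyzed" with a t test.
- **Adjusted model.** "When a change in a selected outcome variable is identified, this change will be modeled using linear regression adjusted for possible confounders".

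Three other sections bear on this. Primary Outcome Measure defines the outcome as a between-group difference in HbA1c change at 4 months and 1 year. Trial Population and Recruitment requires patients to "have an HbA1c level >7.0" (percent). The Overview under Evaluation Measures states: "We intend to evaluate a large number and variety of outcomes".

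**The concern.** The adjusted regression is the plan's own remedy for chance imbalance, yet it is produced only after a look at the outcome. The sentence leaves open what counts as identifying a change (the ANOVA, a post hoc test or a within-group t test) and which outcomes are selected.

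Two things are at stake. First, if imbalance masks an effect, the crude result is null, the trigger does not fire, and the correction promised earlier in the section is not made. Second, if the trigger is a significant between-group result, the adjusted estimates that get reported are those that happened to come out large.

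A separate, smaller matter is the inferential use of within-group t tests in a trial whose primary outcome is a between-group contrast. HbA1c can fall in an arm for reasons unrelated to the app or the counseling, and selection on a raised value is one of them.

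**Working it through.** **Inputs from the documents.** Power Analyses: "a significance level of 5" percent, "a two-tailed significance test", "statistical power of 80" percent, "Given an effect size of 0.35", SD 0.5, 34 per group. Results: 26 of 151 lost, so (151 − 26)/3 = 41.7, taken as 42 per arm.

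**The plan's own figure.** n = 2(1.960 + 0.842)² × (0.5/0.35)² = 32.04, that is 33 per group by the normal approximation; the exact t calculation gives 33.02, rounded up to 34. The stated 34 is reproduced if 0.35 is a raw HbA1c difference. Read as a standardised effect, it would need 129 per group.

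**Step 1: the two statements on adjustment.** One says that variables found to differ will be adjusted for. The other fits the adjusted model only when a change is identified. After a null crude result the first requires an adjusted analysis and the second does not provide one.

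**Step 2: selection if the trigger is a significant two-arm comparison.** SE = 0.5 × √(2/42) = 0.109. The critical t on 82 df is 1.989, so an observed difference must exceed about 1.989 × 0.109 = 0.217 to be significant. True differences of 0.10 and 0.20 both lie below that. With θ = δ/SE and c = 1.989,

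mean estimate given significance ≈ δ + SE × [φ(c − θ) − φ(c + θ)] / P(significant).

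| True δ | θ | P(significant) | Calculation | Mean when significant | Excess |
|---|---|---|---|---|---|
| 0.10 | 0.917 | 0.15 | 0.10 + 0.109 × (0.2244 − 0.0059)/0.148 | 0.26 | about 160% |
| 0.20 | 1.833 | 0.44 | 0.20 + 0.109 × (0.3941 − 0.0003)/0.441 | 0.30 | about 48% |
| 0.35 | 3.208 | 0.89 | 0.35 + 0.109 × 0.1899/0.887 | 0.37 | about 7% |

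Simulation gives the same values (0.26, 0.30, 0.37). Strictly, they describe the crude estimate selected on its own significance. The adjusted estimate comes from the same patients and inherits the excess to the extent that it tracks the crude one.

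**Step 3: other possible triggers.** Simulation of three arms, 42 per arm, SD of change 0.5, assumed correlation 0.5 between time points, 20,000 runs:

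- No condition: true 0, 0.15 and 0.35 average 0.00, 0.15 and 0.35, with 5% type I error.
- ANOVA significant at 1 year: true 0.15 averages 0.26, and true 0.35 averages 0.365.
- Within-group change significant in one intervention arm at 1 year: true 0.15 averages 0.21 with no fall common to all arms, 0.17 with a common fall of 0.1, and 0.15 with a common fall of 0.2.
- Any of the six within-group HbA1c tests significant, no treatment effect, common fall 0.2: the trigger fires in 99.7% of trials, and the between-arm estimate averages 0.00 with a 5.0% false-positive rate.

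**Step 4: what a within-group test can show.** With no change at all, at least one of six independent tests is significant with probability 1 − 0.95⁶ = 26%; simulation with correlated time points gives about 25%. Entry above 7.0% adds regression to the mean. The documents give no HbA1c mean, SD or retest correlation, so as an illustration assume a source mean of 7.2, SD 1.0, correlation 0.9 to 0.7, and the qualifying value used as baseline.

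- Mean among entrants: 7.2 + 0.675 = 7.875.
- Expected fall: (1 − ρ) × 0.675 = 0.07, 0.14 and 0.20 at ρ = 0.9, 0.8 and 0.7.
- Implied SD of change: √[(1 − ρ)² × 0.409 + (1 − ρ²)] = 0.44, 0.61 and 0.74, where 0.409 is the variance of the entry value among entrants.
- Probability that one arm of 42 shows a significant change with no treatment effect: about 16%, 29% and 41%.

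Over a wider assumed range (mean 7.0 to 8.0, SD 0.8 to 1.4, correlation 0.6 to 0.9), the expected fall is 0.02 to 0.45 and the probability 6% to 68%.

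**The case against.** The strongest reply is that the primary comparison is not conditional at all. The crude ANOVA of HbA1c change is planned whatever it shows, and it answers the declared primary question. This stands: a reader might infer that every reported effect is selected and inflated, and the text does not support that. Only the adjusted estimates are affected.

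A reader might also infer that regression to the mean makes the within-group tests significant, opens the way to the regression and so inflates the effects. The text does not say that the t tests are the trigger. If they were, a fall common to randomised arms would make the trigger fire almost always, which lessens selection (Step 3). The inflation in Step 2 comes from a between-group trigger, which a common fall does not touch. Nor does the article say that significance in one arm and not in another will be read as an effect.

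Some larger figures should be resisted. Holding the SD of change at 0.5 under the assumptions of Step 4 would push the within-arm probability to 73%, but those assumptions imply SDs of 0.44 to 0.74 and a top value of 41%. All of these shrink if baseline was measured separately from the qualifying value. One could also count 18 questionnaire scales × 2 times × 3 pairs = 108 tests, with 5.4 expected false positives at 5%. That is a multiplicity question, it presumes uncorrected pairwise tests, and the change proposed here would leave the count as it is.

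Finally, a journal article may leave the list of modeled outcomes and the definition of a change to an analysis plan. That excuses the missing definitions, but not the rule: the article states the condition, and an analysis plan that follows it would carry the flaw over.

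**Conclusion.** The point holds for the adjusted estimates. Whether they exist depends on the outcome result, through an undefined trigger and an undefined set of outcomes, and this contradicts the section's own unconditional statement on adjustment. The loss of correction for imbalance after a null crude result follows from the wording alone.

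The size of the inflation depends on the trigger. With a significant between-group test, 42 per arm, SD 0.5, and an adjusted estimate close to the crude one, it is large for effects smaller than planned (0.20 reported as about 0.30, 0.10 as about 0.26) and small at the planned 0.35 (about 0.37). With a within-group trigger and an appreciable common fall, it is close to nil.

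The within-group t tests are not evidence of an effect of the app or the counseling. How far regression to the mean moves them rests on assumptions that the documents do not supply, and it does not bias the contrast between arms. Because the crude primary comparison is safe from this selection, the matter should be fixed but does not undermine the main analysis.

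**What to change.** Replace the conditional sentence in Statistical Analysis with:

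> The adjusted between-group model will be fitted and reported with 95% CI for the primary outcome and each listed secondary outcome at 4 months and 1 year, whatever the crude result.

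This also removes the conflict with the statement on baseline differences. Present within-group changes as descriptive means with CI, and state that they neither count as evidence of effect nor trigger modeling.

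The cost is the change of wording and a few more table rows. No further data are needed and the sample size is unaffected.
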